## **Rescue Treatment**

Patients failing in any arm within 14 days of treatment will be treated with quinine 10mg/kg/dose every 8 hours for 7 days as per National Guidelines [37]. This treatment will be administered orally unless the patient has persistent vomiting, in which case he/she will be referred to the nearest hospital. Patients presenting after 14 days of treatment will receive the same therapy.

**Concomitant Treatment** Using standard clinic procedures, clinic personnel will administer supportive treatment to patients as necessary:

- **Antipyretics** will be given for temperatures  $> 38^{\circ}\text{C}$  as per national policy. All patients enrolled in the study will be given two additional doses of paracetamol for use at home. Patients/parents/guardians should be instructed in the use and application of tepid sponging and fanning as per national policy.
- **Ferrous Sulfate/ Folate** will be given to all children with hemoglobin  $<11$  mg/dl as per Integrated Management of Childhood Illness (IMCI) Guidelines
- **Anti-helminthics** will be given to children with hemoglobin  $<11$  mg/dl over one year of age as per IMCI Guidelines

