**Exclusion criteria for enrollment:**

1. General danger signs or symptoms of severe malaria (see Annex II)
2. Signs or symptoms of severe malnutrition, defined as weight-for-age  $\leq 3$  standard deviations below the mean (NCHS/WHO normalized reference values; see Annex III)
3. Slide confirmed infection with any other *Plasmodium species*. besides *P. vivax* mono-infection
4. Acute anemia, defined as Hg < 8 g/dl
5. Known hypersensitivity to any of the drugs being evaluated
6. Presence of febrile conditions caused by diseases other than malaria
7. Serious or chronic medical condition by history (cardiac, renal, hepatic diseases, sickle cell disease, HIV/AIDS)
8. Pregnant or breastfeeding women.
9. History of hemolysis or severe anemia
10. Regular medication, which may interfere with antimalarial pharmacokinetics (Annex IV)

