### **Laboratory Evaluations:**

2. Urine pregnancy test will be conducted on all women aged 13-49 and anyone testing positive will be excluded.
3. Those enrolled will have a second finger prick performed to assess for the following:
  - Thin smear will be used to verify parasite species and thick smear to conduct a formal parasite count. Two qualified microscopists will read all the slides independently. Blood smears with discordant results (differences between the two microscopists in species diagnosis, in parasite density of > 50% or in the presence of parasites) will be re-examined by a third, independent microscopist, and parasite density will be calculated by averaging the two closest counts.
  - Hemoglobin measurement (HemoCue™ Hb 301HemoCue, Angelholm, Sweden) will be carried out and those with hemoglobin <8g/dL will be excluded.
  - Filter paper will be obtained for the purpose of genotyping to differentiate identical vs. different genotypes, potential molecular testing for resistance markers, and gametocyte testing. G6PD testing using the NADPH fluorescent spot test will be conducted at the end of each day. The NADPH fluorescent spot test is a qualitative test and those determined to be G6PD deficient will not be given primaquine.
4. Patients testing smear positive for Pv will receive AL, at one site and CQ at the other site. After G6PD testing results are available, the patients not found to be G6PD deficient will be randomized to either AL alone or AL+PQ at one study site and CQ alone or CQ+PQ at the other site. Those found to be G6PD deficient will remain in either the AL or CQ alone arms. The study will not be blinded, although microscopists reading blood films will not be aware of which arm a participant is from.
5. On day 0, each patient will receive the morning dose of treatment (AL or CQ) medication under direct observation and will be monitored for vomiting for 60 minutes. The patient or parent will be given the evening dose (for AL only) to administer at home. Each patient will return on days 1 and 2 (and up to 14 days for those in the PQ arms) for subsequent doses. Those in the primaquine arms will return on every second day on days 2-16 for directly observed therapy. Clinical reassessments will be made on days 1- 3, 7, 14, 21, 28, 35, 42, and then monthly (see Annex V and VI for a table of scheduled procedures).

Participants will be given 35 Ethiopian Birr for each visit to cover their travel expenses (this is

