enough to cover round-trip transportation by bus to the clinic for one adult; parent traveling with the enrolled child requiring their own seat (age >6 years) will receive 50 Birr). Patients will be advised to return on *any* day during the follow-up period if symptoms return and not to wait for scheduled visit days (although they will not be reimbursed for extra visits unless found to be legitimate visits). Patients who do not present to the facility for follow-up visits will be followed at home. This is standard for in vivo studies based on the WHO protocol, but is not the standard for routine care. Typically, for patients not enrolled in a study, the patients would be given all the doses of the medicine to administer at home, and no follow-up would be scheduled. The patient would be told to return if the child did not improve.

6. Blood films (thick and thin) for parasite count will be obtained and examined at each visit and on any other day if the patient spontaneously returns with fever or worsening symptoms.

7. Hemoglobin status will be measured on days 0, 3, 7, 14, 28, 42 and any other unscheduled visits.

8. **Drug level testing.** DBS will be collected on day 7 for lumefantrine plasma level [39], day of recurrent parasitemia for chloroquine levels [40], and day 7 and 14 for primaquine levels. Drug level testing involves liquid chromatography and these tests will be conducted at CDC Atlanta.

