9. **Molecular testing.** A filter paper blood spot will be collected on days 0 and after day 3 in case of recurrent parasitemia for an array of parasite molecular testing including genotyping, resistance drug markers, parasite genome sequencing, and for gametocytes. In *P. falciparum* malaria primaquine accelerates clearance of gametocytes and artemisinin derivatives prevent gametocyte development. However, in *P. vivax* malaria effect of these drugs on gametocyte carriage remains unclear due to limited studies. Therefore, we will examine gametocytemia by blood smear and measuring Pvs25 using reverse –transcript quantitative PCR tool in the smear positive DBS from day 0 and follow up visits. Lastly, for any patients noted to have G6PD deficiency or a greater than 2.4g/dL drop in hemoglobin, their DBS sample will be tested for genetic variants of G6PD deficiency. The molecular testing will be conducted in Addis Ababa, Ethiopia, by Ethiopia Health and Nutrition Research Institute (EHNRI). If EHNRI cannot accomplish this in a timely manner, CDC Atlanta, will serve as a back-stop institution. All samples will have the study ID number and date of collection, but no other personal identifiers. The logbook that links the study ID number to the patient will be kept at the study site locked in a cabinet when not in use during the study enrollment period. After the completion of the study, this logbook will be stored in a locked cabinet in Addis Ababa at ICAP’s office. DBSs will not be used for non-malaria-related tests including HIV.

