##### **Adequate clinical and parasitological response**

- absence of parasitaemia on day 28 (day 42), irrespective of axillary temperature, in patients who did not previously meet any of the criteria of early treatment failure, late clinical failure or late parasitological failure

*P. vivax* infections that recur after drug treatment can have 1 of 3 etiologies: 1) recrudescence, 2) reinfection, or 3) relapse arising from the dormant liver stage (hypnozoites). In order to differentiate the recurrent parasitemias as identical vs. different from the original infection, a genotypic analysis will be performed by PCR including characterizing microsatellite markers to assess recrudescence from reinfection and for drug resistance markers. Molecular testing for gametocytes will also be conducted on any smear positive days. Those who fail in the chloroquine arm will have CQ levels tested from the already collected filter paper. Lumefantrine level on day 7 will be measured for those receiving AL treatment from collected filter papers. Patients noted to have G6PD deficiency by the fluorescent spot test and those with hemoglobin drop of >2.4g/dL will undergo additional G6PD genotyping.

**Valid end-points** include treatment failure, completion of the follow-up period without treatment failure, loss to follow-up, withdrawal from study (voluntary or involuntary, and protocol violation). Loss to follow-up occurs when, despite all reasonable effort, an enrolled patient who does not attend the scheduled visits, cannot be found. Patients who withdraw from the study during the treatment period (days 0-2) will be treated with CQ according to the national policy. They will be referred back to the clinic to continue with care.

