## EMERGENCY CARE

Any patient with treatment failure or recrudescence will receive quinine 10mg/kg/dose every 8 hours for 7 days. This will be given orally unless the patient has persistent vomiting, in which case the patient will be referred to the nearest hospital to receive IM/IV therapy.

Patients with signs of severe malaria (altered mental status, coma, convulsions, hemoglobin <5g/dl, respiratory distress, circulatory collapse, or abnormal bleeding), persistent vomiting or severe side effects will be hospitalized and receive parenteral therapy with artesunate (or quinine if not available) and relevant supportive treatments, according to National Guidelines.

Any participant who develops urticaria or difficulty breathing following administration of the treatment drug will be treated with diphenhydramine or chlorpheniramine and will be withdrawn from the study. In addition, patient and or their parents, caretakers and family members will be counseled that the patient should not receive additional doses of the antimalarial they were given. These patients will be treated with oral quinine for seven days as per the rescue protocol.

Adult patients and parents with children in the study will be encouraged to return to the clinic for any fever or other signs of illness on any day during the follow-up period, allowing for early detection and treatment of illness before it becomes severe. Any hospitalization which occurs during the follow-up period will be paid for by the study.

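### The haemoglobin trigger for iron/folate and for anti-helminthics in children is printed in mg/dl instead of g/dl, so as written no enrolled child can meet it

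*Protocol*

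**What the plan says.** The Concomitant Treatment list, under Rescue Treatment in the protocol, makes two supportive treatments for children depend on a haemoglobin level. Ferrous sulfate/folate "will be given to all children with hemoglobin $<11$ mg/dl as per Integrated Management of Childhood Illness" guidelines. Anti-helminthics "will be given to children with hemoglobin $<11$ mg/dl over one year of age as per IMCI Guidelines".

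Elsewhere haemoglobin is always given in g/dl:

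- Exclusion criteria for enrollment, item 4: "Acute anemia, defined as Hg < 8 g/dl".
- Laboratory Evaluations, item 3: "those with hemoglobin <8g/dL will be excluded".
- Laboratory Evaluations, item 9 (molecular testing): G6PD variants are tested after "a greater than 2.4g/dL drop in hemoglobin".
- End-points, in the text after the definition of adequate clinical and parasitological response: patients with a "hemoglobin drop of >2.4g/dL will undergo additional G6PD genotyping".
- Emergency Care: "hemoglobin <5g/dl" is listed among the signs of severe malaria.

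On timing, Laboratory Evaluations, item 7, states: "Hemoglobin status will be measured on days 0, 3, 7, 14, 28, 42 and any other unscheduled visits". Annexes V and VI add a measurement at month 12. No part of the protocol restates the treatment trigger in another unit or corrects it.

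**The concern.** A cut-off of 11 mg/dl does not fit the protocol's own haemoglobin scale. Children are excluded below 8 g/dl and treated as severe malaria below 5 g/dl, so a supportive-care trigger at 0.011 g/dl sits beneath both and could never be reached. The same unit appears in two separate bullets, so it does not look like a fault of text extraction.

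What is at stake is the written care rule for children with anaemia. A child may enter with haemoglobin between 8 and 11 g/dl, or may fall below 11 g/dl later. As printed, the rule gives neither iron/folate nor anti-helminthics to such a child. The trial also gives primaquine, for which the protocol names haemolytic anaemia in G6PD deficiency as the most important adverse effect, so its haemoglobin instructions ought to be right. No bias in the comparison of haemoglobin between the primaquine and no-primaquine arms is claimed.

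**Working it through.** The check is a unit conversion and a comparison with the protocol's other limits.

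**Inputs**

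| Threshold | Place in the protocol | As printed |
|---|---|---|
| Iron/folate trigger | Concomitant Treatment | <11 mg/dl |
| Anti-helminthics trigger | Concomitant Treatment | <11 mg/dl |
| Entry exclusion | Exclusion criteria, item 4; Laboratory Evaluations, item 3 | <8 g/dl |
| Fall prompting G6PD genotyping | Laboratory Evaluations, item 9; End-points | >2.4 g/dl |
| Severe malaria | Emergency Care | <5 g/dl |

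**Step 1. Convert the printed trigger.** With 1 g = 1,000 mg, 11 mg/dl ÷ 1,000 = 0.011 g/dl.

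**Step 2. Compare it with the entry limit.** 8 g/dl = 8,000 mg/dl, and 8 ÷ 0.011 ≈ 727. The lowest haemoglobin allowed at entry is about 727 times the printed trigger.

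**Step 3. Compare it with the severe-malaria limit.** 5 g/dl = 5,000 mg/dl, and 5 ÷ 0.011 ≈ 455. A child already classed as having severe malaria on haemoglobin could still be hundreds of times above the trigger. Steps 2 and 3 show that the printed value is impossible; they do not measure harm.

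**Step 4. Apply the rule as printed.** Every enrolled child has at least 8 g/dl at entry, and no attainable value in follow-up approaches 0.011 g/dl. The share of enrolled children who qualify is 0% at every visit.

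**Step 5. Apply the rule in g/dl.** 11 g/dl = 11,000 mg/dl, which lies above the entry limit. At entry the rule covers 8 to below 11 g/dl (8,000 to below 11,000 mg/dl). In follow-up it covers any child below 11 g/dl. The protocol does not give the share of children in that range, so the number affected cannot be stated.

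**Step 6. Check consistency.** All five other statements of a haemoglobin threshold use g/dl (two for entry, two for the fall, one for severe malaria). Only the two treatment bullets use mg/dl.

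**The case against.** The strongest reply is that nobody could act on the printed value. It is physiologically impossible, the same staff apply limits of 8 and 5 g/dl, and they are licensed clinicians with about a week of study-specific training. Both bullets defer to the IMCI guidelines, and the sentence introducing them leaves supportive care to usual clinic practice and to need. The bullets say when treatment is given and do not forbid it otherwise, so a child with anaemia could still be treated. On this view the point is editorial.

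Most of this stands, and it limits the weight of the point. A correct reading by staff is very likely, and actual harm is unlikely. It does not make the instruction right: the protocol chose to print its own threshold, and that threshold is wrong.

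Two narrower remarks also stand. The bullets do not say at which visits the trigger applies, so applying it during follow-up is a reading, though a natural one given the repeated haemoglobin measurements. And the IMCI guideline is not at hand, so the documents support a correction of the unit but no check of the figure 11 itself.

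**Conclusion.** The point holds. Both bullets give a treatment threshold that is too low by a factor of 1,000 and that no enrolled child can meet. That the intended unit is g/dl follows from the protocol alone: every other haemoglobin threshold uses it, and 11 g/dl falls sensibly above the entry limit of 8. The conclusion assumes that the figure 11 is as intended.

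The weight is low. This is a unit slip in a supportive-care instruction for children, and staff would very probably read through it. Sample size, endpoints and planned analyses are untouched. It is worth correcting because it is an operative clinical rule and the correction is certain.

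**What to change.** In the Concomitant Treatment list, change the unit from mg/dl to g/dl in both the ferrous sulfate/folate bullet and the anti-helminthics bullet, so that each trigger is haemoglobin below 11 g/dl. The cost is one unit corrected in two lines; nothing in the design, visit schedule or analysis changes.

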## **Population**

### **Description and source of population and catchment area**

The population of interest consists of patients aged above 1 year living in malarious areas diagnosed with uncomplicated *P. vivax* malaria consulting at the health facility, who or whose parents or guardians give permission for study inclusion. Children cannot be excluded as they represent a high-risk population for malaria and it is imperative that the first-line antimalarials are effective in this group. For logistical reasons, only patients living near the enrolling health care facilities will be included (within 20 km), as we plan to visit the houses of those patients who do not return for scheduled follow-ups.

### **Initial screening *inclusion* criteria:**

- Slide-confirmed infection with *P. vivax*
- Age  $> 1$  year
- Lives within 20 km of the enrolling health facility

### **Inclusion criteria for enrollment:**

1. Meet screening inclusion criteria
2. Weight  $\geq 5.0$  kg
3. Axillary temperature  $\geq 37.5^{\circ}\text{C}$  or history of fever during the previous 48 hours
4. Patient or caregiver agrees to all finger pricks and return visits.

**Exclusion criteria for enrollment:**

1. General danger signs or symptoms of severe malaria (see Annex II)
2. Signs or symptoms of severe malnutrition, defined as weight-for-age  $\leq 3$  standard deviations below the mean (NCHS/WHO normalized reference values; see Annex III)
3. Slide confirmed infection with any other *Plasmodium species*. besides *P. vivax* mono-infection
4. Acute anemia, defined as Hg < 8 g/dl
5. Known hypersensitivity to any of the drugs being evaluated
6. Presence of febrile conditions caused by diseases other than malaria
7. Serious or chronic medical condition by history (cardiac, renal, hepatic diseases, sickle cell disease, HIV/AIDS)
8. Pregnant or breastfeeding women.
9. History of hemolysis or severe anemia
10. Regular medication, which may interfere with antimalarial pharmacokinetics (Annex IV)

**Sampling, sample size and statistical power****Sample size determination:**

The design of the study is to compare the addition of PQ to AL or CQ alone. From our previous efficacy study, CQ alone showed a success rate of 68% at day 42 (null hypothesis). It will be assumed under the alternative hypothesis that the addition of PQ will decrease the chance of relapse by at least 60% resulting in a success rate of 87%. Group sample sizes of 97 in each group will achieve 90% power to detect a difference between group proportions of 19% using the two-sided Z-test with pooled variance test statistic. The significance level of the test was targeted at 0.05. Adjusting the alpha level to 0.025 for multiple comparisons will increase the sample size to 118 in each group. The AL arm showed even a lower efficacy at day 42 in our previous study of 58%. Using this lower success rate of 58% seen with AL at day 42, resulted in a smaller required sample size of 68. Taking into account 10-20% loss to follow-up at 42 days, a sample size of 120 subjects for each treatment was determined to be optimal.

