## **END-POINTS**

### **Outcomes and minimal differences**

#### **Efficacy end points**

The primary outcome of this study will be to estimate the efficacy of AL compared to AL+PQ, and CQ compared to CQ+PQ against vivax malaria at Day 28/42.

In addition, any episode of vivax parasitemia during the one year follow-up following parasite clearance will be considered a recurrence. Each recurrence will be treated in the same fashion as the initial episode, the patient remains in the treatment arm he or she has been randomised to for the duration of the follow-up period.

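### The CQ comparison is sized on a flat split of alpha to 0.025; a Holm rule keeps the same 5% family-wise error and would recover about 5 to 6 points of CQ power without more patients, provided PQ also works with AL

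*Protocol*

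**What the plan says.** The section on efficacy end points sets two primary comparisons: "The primary outcome of this study will be to estimate the efficacy of AL compared to AL+PQ, and CQ compared to CQ+PQ", read at day 28/42.

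The section on sample size determination starts from the CQ pair, with 68% success on CQ alone and 87% with PQ, a two-sided pooled Z-test and 90% power. On the level it says "The significance level of the test was targeted at 0.05", which leads to 97 per group. It then adds "Adjusting the alpha level to 0.025 for multiple comparisons will increase the sample size to 118 in each group". For AL it says "Using this lower success rate of 58% seen with AL at day 42, resulted in a smaller required sample size of 68", without giving an alpha or an AL+PQ rate. It closes with "Taking into account 10-20% loss to follow-up at 42 days, a sample size of 120 subjects for each treatment was determined to be optimal".

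The data analysis plan lists failure proportions at days 28 and 42 with 95% confidence intervals, by a per-protocol and a survival method. It gives no test level and no multiplicity procedure. The 0.025 in the sizing paragraph is therefore the only multiplicity provision in the protocol.

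**The concern.** Dividing 0.05 by two is a single-step Bonferroni split. Holm tests the smaller of the two p-values at 0.025 and, if that is significant, the larger at 0.05. It rejects everything that the split rejects and sometimes more, and it controls family-wise error at the same 5% without any assumption about dependence.

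The difference matters here because the two comparisons are unequally powered. By the protocol's own figures CQ is the harder one (118 per group, against 68 for AL). If the AL comparison usually succeeds, Holm usually releases the full 0.05 to CQ. CQ is also the national first-line drug for vivax malaria, so this pair bears most directly on policy. With a significant AL result, a CQ p-value between 0.025 and 0.05 would count as a success under Holm and not under a flat split.

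**Working it through.** **Inputs.** From the sample size section: CQ 0.68 against 0.87; AL alone 0.58; 120 enrolled per arm; 10-20% loss, so 120 × 0.90 = 108 and 120 × 0.80 = 96 evaluable. The protocol gives no AL+PQ rate, so three values are used:
- 0.83: the 60% cut applied to 42% failure, 1 − 0.4 × 0.42 = 0.832
- 0.77: the same 19-point difference as for CQ
- 0.58: no PQ effect with AL

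**Reproducing the plan's figure.** n = [z(1−α/2)·√(2p̄q̄) + z(0.90)·√(p₁q₁ + p₂q₂)]² / (p₁ − p₂)².

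For CQ at α = 0.025, p̄ = 0.775: [2.2414 × √0.34875 + 1.2816 × √0.3307]² / 0.19² = (1.3237 + 0.7370)² / 0.0361 = 117.6, so **118**, as stated.

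The 97 is reproduced at α = 0.05 with the unrounded rate 0.872 (0.87 gives 100). The AL figure of 68 is reproduced with 0.58 against 0.83 at α = 0.05; at 0.025 the same effect needs 81.

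**Power after loss.** Exact binomial power of the two-sided pooled Z-test:

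| Evaluable per arm | CQ at 0.025 | CQ at 0.05 | AL at 0.025 (AL+PQ 0.83) | AL at 0.025 (AL+PQ 0.77) |
|---|---|---|---|---|
| 108 | 0.8795 | 0.9286 | 0.9703 | 0.7805 |
| 96 | 0.8360 | 0.8970 | 0.9504 | 0.7272 |

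The two pairs contain different patients, so they are taken as independent:

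Holm power for CQ = P_CQ(0.025) + [P_CQ(0.05) − P_CQ(0.025)] × P_AL(0.025).

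- AL+PQ 0.83: at 108, 0.8795 + 0.0491 × 0.9703 = 0.927; at 96, 0.8360 + 0.0610 × 0.9504 = 0.894.
- AL+PQ 0.77: at 108, 0.8795 + 0.0491 × 0.7805 = 0.918; at 96, 0.8360 + 0.0610 × 0.7272 = 0.880.
- No PQ effect with AL: the last factor is about 0.024, giving 0.881 at 108 and 0.8375 at 96, practically the flat-split values.

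**Winning both comparisons (AL+PQ 0.83).** Flat: 0.8795 × 0.9703 = 0.853 at 108 and 0.8360 × 0.9504 = 0.795 at 96. Holm: 0.914 and 0.872.

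**Cross-checks.** Normal-approximation power gives CQ 87.1% and 82.5% flat, and 92.1% and 88.6% under Holm (AL+PQ 0.83). Simulation with 400,000 replicates puts Holm's family-wise error at about 0.048 to 0.050.

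**The case against.** **No decision rule is stated.** A reader might infer that the protocol commits to testing each comparison at a flat 0.025. It does not. The 0.025 serves to size the CQ pair, the AL figure of 68 matches 0.05 under the 60% assumption, and the analysis section fixes no test level. Sizing at 0.025 is compatible with a later Holm test, whose first step is at 0.025, and an analysis plan that is not shown could specify one. This stands, and it limits the point to the sizing choice and the power quoted for it.

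**A Bonferroni split is valid.** This also stands. Nothing here inflates the error rate.

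**The gain is conditional.** A reader might infer that Holm restores 90% CQ power whatever happens. The documents do not support that: the gain needs the AL comparison to succeed, the AL+PQ rate is not given, and at 20% loss Holm ends just under 90% even with AL+PQ at 83%.

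**Holm needs one p-value per pair.** The primary outcome is read at day 28/42 and analysed by two methods, so Holm alone does not settle multiplicity. This stands and is taken into the fix.

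**Intervals may disagree with the decision.** With a CQ p-value between 0.025 and 0.05, a 97.5% interval would include no difference while Holm declares success. This is a real but small cost in a trial that frames its primary aim as estimation.

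**The shortfall for losses is a separate matter.** Allowing for 10-20% loss on 118 needs 118/0.90 = 132 to 118/0.80 = 148 per arm, not 120. Holm softens the consequence but does not correct that step.

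**Conclusion.** The point holds as an efficiency improvement. The only multiplicity provision in the protocol is a flat 0.025 in the sizing of the CQ comparison. At that level, and after the protocol's own losses, CQ power is about 84-88% instead of 90%. Holm, at the same nominal 5% family-wise error and with no added patients, gives about 89-93% if AL+PQ success is 83%, 88-92% if it is 77%, and essentially no change if PQ does nothing with AL. It lowers power in none of these cases.

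The figures rest on the protocol's success rates, equal arms, loss that removes patients entirely from the analysis, independent pairs, and the assumed AL+PQ rate.

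**What to change.** In the sample size section, state that the AL and CQ comparisons at the primary time point (day 42, the day used for sizing) will be tested by the Holm procedure at family-wise 0.05: the smaller p-value at 0.025 and, if significant, the larger at 0.05. Name the single analysis that supplies each p-value.

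Restate CQ power after 10-20% loss as about 84-88% at a flat 0.025 and about 89-93% under Holm, with the AL+PQ assumption of 83% written out and the results for 77% and for no effect beside it. Add a line explaining how the reported interval relates to the Holm decision when the two differ.

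The cost is a few sentences and no patients. The rule should be fixed before outcome data are seen, since a later switch would look driven by results.

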## DATA HANDLING AND ANALYSIS

### **Data analysis plan, including statistical methodology and planned tables and figures**

SAS 9.3 (Cary, NC) as well as the WHO drug efficacy tools provided at <http://www.who.int/malaria/toolsformonitoring.html> will be used for data management and analysis. Data will be analyzed using two methods: **per protocol analysis**, where patients who were withdrawn from the study or who were lost to follow-up are excluded, and **survival analysis**, where all enrolled patients are included in the analysis until the last day before drop-out. In addition to voluntary withdrawals or treatment non-compliance, patients will be considered for the analysis as withdrawn if the PCR results are unclassifiable.

The final analysis will include:

- A description of the patients screened, and the distribution of the reasons for exclusion.
- A description of the patients included in the study.
- The proportion of patients lost to follow-up or withdrawn and the distribution of reasons for withdrawal.
- The proportion of treatment failures in each Pv arm at day 28 and day 42 with 95% confidence intervals using both methods of analysis.
- Frequency of side effects, severe malaria, anemia, and hospitalizations by treatment arm.
- Comparison in absolute means and relative changes in hemoglobin concentration during follow-up after treatment
- Comparison of number of recurrent parasitological vivax episodes after initial parasite episode.

**Data collection:** Data will be collected and recorded at the health facility by one of the trained staff members. All data entry forms will be checked for completeness. Laboratorians may complete brief reports on laboratory findings to share with clinicians who will transfer these results to the case report form of the appropriate patient, the laboratory results will be entered into an Excel database.

**Information management and analysis software:** Microsoft Excel (Redmond, Washington) will be used for double entry of laboratory data and clinical data. SAS 9.3 (Cary, NC) will be used for data analysis.

**Data entry, editing, handling, storage and disposition:** Some open-ended data including the names of specific drugs or diagnoses will be coded prior to data entry. A list of standard codes for these fields will be developed by hand once collection of data is complete. All forms will then be coded and checked by 2 different team members.

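### The required sample size of 68 for artemether-lumefantrine (AL) appears to omit the 0.025 multiplicity adjustment, and the protocol does not say which alpha decides the two primary comparisons

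*Protocol*

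**What the plan says.** All the planning figures are in the protocol's sample size determination. The CQ comparison starts from the earlier study, where "CQ alone showed a success rate of 68% at day 42 (null hypothesis"), and assumes that "the addition of PQ will decrease the chance of relapse by at least 60% resulting in a success rate of 87" per cent. On that basis "Group sample sizes of 97 in each group will achieve 90% power", "using the two-sided Z-test with pooled variance test statistic". On the error rate it says "The significance level of the test was targeted at 0.05", and next: "Adjusting the alpha level to 0.025 for multiple comparisons will increase the sample size to 118 in each group". The AL sentence follows: "Using this lower success rate of 58% seen with AL at day 42, resulted in a smaller required sample size of 68". It gives neither an alpha nor a success rate for AL+PQ. After allowing for 10-20% loss by day 42, the section settles on 120 subjects per treatment.

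The End-points section makes both PQ comparisons the primary outcome (AL against AL+PQ, CQ against CQ+PQ). For this outcome the data analysis plan lists "The proportion of treatment failures in each Pv arm at day 28 and day 42 with 95% confidence intervals" and gives no test level.

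**The concern.** Reducing alpha from 0.05 to 0.025 is the usual split across two comparisons, so it should apply to both. The CQ size of 118 carries it. The AL size of 68 is the next figure given and is called smaller, so a reader will take it to be on the same footing. If it is not, one of the two stated requirements is on the wrong level.

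The wording also leaves the decision level open. The text says that 0.05 was the target and that adjusting will raise the sample size, but not that the adjusted level was adopted for the tests. The results are meant to inform national treatment guidelines, so the threshold for claiming a benefit of PQ should be fixed before any data are seen.

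**Working it through.** **Inputs from the sample size section.** Two-sided Z-test with pooled variance; 90% power; CQ alone 68%; CQ with PQ 87% (exactly 1 − 0.4 × 0.32 = 0.872); AL alone 58%; 10-20% loss; 120 per arm.

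**Assumption.** The AL+PQ rate is not stated. Applying the same 60% reduction gives 1 − 0.4 × 0.42 = 0.832, or 83% rounded.

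**Formula, per group.** n = [z(1−α/2)·√(2p̄(1−p̄)) + z(0.90)·√(p1(1−p1) + p2(1−p2))]² / (p1 − p2)², where p̄ is the mean of p1 and p2. Here z(0.90) = 1.2816, and z(1−α/2) is 1.9600 at α = 0.05 and 2.2414 at α = 0.025.

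**CQ, the plan's own figures.**
- 0.68 against 0.872, α = 0.05: (1.1556 + 0.7353)² / 0.192² = 97.0. The stated 97 reproduces.
- 0.68 against 0.87, α = 0.025: (1.3237 + 0.7370)² / 0.19² = 117.6, so 118. The stated 118 reproduces.
- The two figures round the PQ rate differently: 0.87 at 0.05 gives 100, and 0.872 at 0.025 gives 115. This does not blur which alpha each belongs to.

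**AL.**

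| AL+PQ rate | α = 0.05 | α = 0.025 |
|---|---|---|
| 0.83 | (1.2641 + 0.7949)² / 0.25² = 67.8, so 68 | (1.4456 + 0.7949)² / 0.25² = 80.3, so 81 |
| 0.832 | 66.6, so 67 | 78.8, so 79 |

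The stated 68 matches α = 0.05. Like for like, the AL and CQ figures are 68 and 97 at 0.05, or 81 and 118 at 0.025. The text sets 68 beside 118.

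**Does the final 120 settle the level?** Inflating for 10% and 20% loss:
- 97/0.9 = 107.8 and 97/0.8 = 121.3, so 108 to 122.
- 118/0.9 = 131.1 and 118/0.8 = 147.5, so 132 to 148.

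With the stated loss, 120 lies within the range for 0.05. With no loss, it just covers 118 at 0.025. So it does not settle the level.

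**What the gap means for a result.** Pooled Z-test with 120 per arm:
- 82 against 96 successes: z = 2.06, p = 0.039.
- 82 against 97 successes: z = 2.22, p = 0.026.

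Both pass at 0.05 and fail at 0.025. The two comparisons use different patients, so the family-wise error is 1 − 0.975² = 4.9% with both at 0.025 and 1 − 0.95² = 9.75% with both at 0.05.

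**Power at 0.025 with 120 enrolled.** Solving the formula for power, with 120 × 0.8 = 96 and 120 × 0.9 = 108 evaluable per arm:

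| Comparison | 96 | 108 |
|---|---|---|
| AL, 58% against 83% | 95% | 97% |
| CQ, 68% against 87% | 83% | 87% |

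**The case against.** Much can be said for the protocol, and part of it stands.

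- **A reader might infer that AL will be tested at 0.05 and CQ at 0.025**, with a family-wise error of 1 − 0.975 × 0.95 = 7.4%. The protocol proposes no such scheme. These are sample-size levels, no alpha is attached to 68, and 0.025 for both is the natural intent. This objection stands.
- **The 0.05 behind 68 is back-calculated.** It rests on carrying over the 60% reduction and rounding to 83%. An AL+PQ rate of 85% would also give 68 at 0.025 (67.1 before rounding up). That is correct, but 85% is not the protocol's stated effect, so the carry-over remains the better reading.
- **The figure of 97 is only the step before adjustment**, not a rival rule. This stands.
- **The 95% intervals in the data analysis plan might be read as setting the test at 0.05.** They are for the failure proportion in each arm, not for a difference between arms, so they set no test level.
- **The 68 drives nothing.** Enrolment is 120 per arm. With 68 evaluable, AL power at 0.025 would be 84%, but that would take about 43% loss, far above the 10-20% planned. AL is not underpowered.
- **An SAP could fix the decision rule.** It could, but the protocol itself states the adjustment and the AL size. An SAP would not correct the 68.

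**Conclusion.** The concern holds in a limited form. On the protocol's own test, power and effect assumption, the AL requirement of 68 appears to leave out the multiplicity adjustment that CQ's 118 includes. At 0.025 it is 81, or 79 with the unrounded rate. This rests on one assumption, that the 60% reduction also applies to AL. Separately, the protocol does not say which level decides the two primary comparisons, so a p-value between 0.025 and 0.05 has no fixed interpretation.

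The error does not threaten the AL comparison, which keeps about 95-97% power at 0.025 after the planned loss. Once 0.025 is confirmed, it is the CQ comparison that falls short: about 83-87% rather than the stated 90%.

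**What to change.** In the sample size section:
1. State that AL against AL+PQ and CQ against CQ+PQ are each tested two-sided at 0.025.
2. Replace 68 with 81 and give the assumed AL+PQ success rate of 83% (79 if 83.2% is used).
3. Keep 120 per arm, but restate power at 0.025 with 96 to 108 evaluable per arm: AL about 95-97%, CQ about 83-87%.

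Any interval used to decide a between-arm difference should be at the matching 97.5% level. The per-arm 95% intervals can stay as description.

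The cost is a few sentences and one corrected figure, with no change in enrolment. The downside is a less favourable stated power for CQ and slightly wider intervals for the two differences. Holding 90% for CQ at 0.025 after 10-20% loss would instead take the 132 to 148 per arm derived above.
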